### Interim analyses {21b}

No interim analyses are prepared for this trial as there are no anticipated problems that are detrimental to the participants.

### Methods for additional analyses (e.g., subgroup analyses) {20b}

There are no additional analyses except for interim analysis for the trial.

### Methods in analysis to handle protocol non-adherence and any statistical methods to handle missing data {20c}

As we mentioned above that we will keep in contact with all participants at least once a week, then we will know the conditions of the participants. Meanwhile, all the participants will be followed at scheduled time to ensure the adherence. The missing data will be handled by a single imputation model for analyses.

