## Primary outcomes

### Fugl-Meyer Assessment (FMA)

Motor function recovery will be assessed using the Fugl-Meyer Assessment (FMA). The FMA rates each sub-item on a scale of 3, with scores of 0 (unable to complete), 1 (partially completed), and 2 (fully completed). The upper limb motor assessment comprises a total of 33 items, with a maximum score of 66.

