### Sample size {14}

The sample size calculation was conducted using G*power software (v3.1.9.2). The effect size of this study was estimated from a study conducted by Kaux et al. [29] who investigated the effects of transcranial direct current stimulation associated with physical therapy in acute stroke patients evaluated by the upper extremity section of the Fugl-Meyer Test, which was determined to be 0.995. The experiment employs a 1:1 simple randomization, n1 = n2. According to a prior difference between two independent means analysis *t* test, with a power of 0.95 and an error probability of 0.05, we applied these values to compute a sample size of *n* = 28. Accounting for a 10% attrition rate, we determined that each group should comprise 31 participants, yielding a total of 62 stroke patients included in the study. It is important to note that all enrolled patients received clinical medications and conventional rehabilitation treatments that were generally uniform.

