## Statistical methods

### Statistical methods for primary and secondary outcomes {20a}

Statistical analysis was conducted using GraphPad Prism version 8.0 and MATLAB 2021a. For continuous variables, the normality of the data distribution in all datasets was assessed using the Kolmogorov–Smirnov test. Continuous variables were presented as mean ± standard deviation (SD) with range values for normally distributed data, or as the medians with the interquartile ranges (IQRs) for non-normally distributed data, respectively. Categorical variables were presented as frequencies and percentages. If the data followed a normal distribution, the difference between the two groups was assessed using Student’s *t* test. If the data did not follow a normal distribution, the Wilcoxon rank test was employed. For categorical variables, a chi-squared test or Fisher’s exact test was utilized for comparison. A significance level of *P* < 0.05 was considered statistically significant.

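### Single imputation followed by ordinary tests ignores imputation uncertainty; depending on the model, the result is a type I error of about 6–8%, a diluted effect, or bias under unequal dropout

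*Protocol article*

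**What the plan says.** Section {20c} fixes the method for missing data in one sentence: "The missing data will be handled by a single imputation model for analyses". It does not say which model, or whether it is fitted within or across arms.

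Section {20a} gives the tests that follow. For continuous outcomes: "If the data followed a normal distribution, the difference between the two groups was assessed using Student’s" *t* test, and "If the data did not follow a normal distribution, the Wilcoxon rank test was employed". Categorical outcomes get a chi-squared or Fisher test, and P < 0.05 "was considered statistically significant". No variance correction for imputed values is mentioned, and section {20b} plans no further analyses other than an interim one.

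The only figure for expected loss is in section {14}: "Accounting for a 10% attrition rate", each arm is set at 31. Outcomes are measured at baseline, after the two weeks of treatment, and at 3 and 6 months.

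**The concern.** Single imputation puts one value in place of each missing score. A test that takes the completed data at face value then counts patients who supplied no outcome and ignores the uncertainty of the filled-in scores. Two kinds of harm are possible. The standard error may be too small, so that P values are too low. Or the imputed values may pull the estimated difference away from the truth. Both would affect the primary comparison of motor function. The protocol states this method positively, so it is more than a detail left to a later document.

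**Working it through.** **1. The plan's own size.** Section {14} takes an effect size "which was determined to be 0.995", "with a power of 0.95 and an error probability of 0.05, we applied these values to compute a sample size of" 28 per group. A two-sided two-sample t test (noncentral t) with d = 0.995, alpha 0.05 and power 0.95 gives 28 per group (power 0.955), so the figure reproduces. Then 28 × 1.1 = 30.8, rounded up to 31 (28/0.9 = 31.1 would give 32; the difference is immaterial here). The planned 10% of 31 is 3.1, so I use 3 missing of 31 per arm, and 6 of 31 (19%) as a higher case.

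**2. Arm-mean imputation, exact.** The difference in means is unchanged and the imputed values add no sum of squares, but the test uses n = 31 instead of n_obs per arm. Hence

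t_imp = t_cc × √[(n/n_obs) × (2n−2)/(2n_obs−2)], where t_cc is the complete-case statistic.

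- 3 missing: (31/28) × (60/54) = 1.230, square root 1.109. The standard error is 1/1.109 = 0.90 of the complete-case value. Rejection occurs when |t| on 54 df exceeds 2.000/1.109 = 1.803, which has probability **7.7%**.
- 6 missing: (31/25) × (60/48) = 1.55, square root 1.245. The standard error ratio is 0.80 and the type I error is **11.5%**.

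**3. Other models, simulated under no effect.** 40,000 trials per cell, 31 per arm, normal outcomes, missing completely at random, equal missing counts per arm, assumed baseline–outcome correlation 0.6, ordinary t test. Each cell gives final score / change score.

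| Handling | 3 of 31 missing | 6 of 31 missing |
|---|---|---|
| Complete cases | 5.0 / 5.0% | 5.0 / 5.1% |
| Arm mean | 7.6 / 6.3% | 11.4 / 7.6% |
| Regression within arm | 6.5 / 7.2% | 8.8 / 10.0% |
| Stochastic regression within arm | 6.8 / 6.9% | 8.5 / 9.4% |
| Hot deck within arm | 7.5 / 6.4% | 10.2 / 7.2% |
| Pooled mean | 5.1 / 5.0% | 4.9 / 5.0% |
| Pooled regression | 5.1 / 5.0% | 5.2 / 5.0% |
| Baseline carried forward, no recovery | 5.0 / 5.0% | 5.1 / 4.9% |
| One fixed poor score | 2.0 / 2.0% | 0.9 / 1.0% |

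With an assumed correlation of 0.7, within-arm models gave 6.6–8.0% and 8.2–12.1%, and pooled models 5.0–5.4%.

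**4. What pooled models do to the estimate.** Missing patients in both arms receive values that carry no arm difference, so the expected difference is multiplied by n_obs/n. For the design effect: 0.995 × 28/31 = 0.90 SD with 3 missing, and 0.995 × 25/31 = 0.80 SD with 6.

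**5. Last value carried forward while patients recover.** Patients enter within one week of onset, and the article's discussion places the plateau of repair after 3 months. Suppose both arms recover by 1 SD (assumed), baseline is carried forward and there is no treatment effect. The bias is then 1 SD × (difference in missing counts)/31.

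- 3 against 3 missing: no bias, type I error 3.8–4.3%.
- 1 against 5 missing: bias 4/31 = 0.13 SD, type I error 6.4–7.4%.
- 0 against 6 missing: bias 6/31 = 0.19 SD, type I error 10.2–12.2%.

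With 0.5 SD recovery the last two become 5.5–5.8% and 6.4–6.9%. This excess comes from bias, not from a small standard error.

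**6. After a fix.** Arm-specific multiple imputation (20 imputations, Rubin's rules with small-sample degrees of freedom, 4,000 trials, correlation 0.6) gives 5.0% with 3 missing and 3.8% with 6.

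**The case against.** The strongest reply is that single imputation does not by itself inflate the type I error. That is correct: pooled models and last value carried forward stay near 5% under equal dropout, and a fixed poor score falls well below it. A reader might infer from {20c} and {20a} that the trial's P values must be too small and its results tilted towards the treatment. The documents do not support this, because the model is unnamed and the direction of error depends on it and on the pattern of dropout. The masking of analysts in section {17a} does not settle whether the model would be fitted by arm.

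A reader might also combine this point with the Trial status section, where recruitment and follow-up both end in 2024, and infer very heavy missingness at 6 months. That needs an assumed accrual pattern and a literal reading of dates that conflict with a 6-month follow-up; it is a separate matter. The article gives no missingness by visit, and its only planning figure is 10%.

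A third reply is that this is a condensed article and an unseen analysis plan may name the model. The missing detail is therefore not held against it. The choice of single imputation is stated in the article itself, however. None of the common versions checked is free of both faults: within-arm models understate the standard error, pooled models dilute the effect, and last value carried forward relies on equal dropout.

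**Conclusion.** The concern holds in conditional form and is of moderate weight. The plan fixes single imputation and then tests the completed data as if they were observed.

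- **Within-arm fitting:** type I error about 6–8% at the planned 10% attrition and about 7–12% with 20% missing.
- **Pooled fitting without arm:** type I error near 5%, with a true difference reduced by about 10% at the planned attrition.
- **Last value carried forward:** near or below 5% with equal dropout, biased when dropout differs between arms.

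The error rates rest on assumptions that the protocol does not give: data missing completely at random, normal outcomes, a baseline correlation of 0.6–0.7, equal missing counts except where stated, and a 0.5–1 SD common recovery for the last case. An unconditional claim that the type I error exceeds 5%, or that the error always favours the treatment, would go beyond the documents.

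**What to change.** Replace the sentence in section {20c} with one of the following:

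- All randomised patients are analysed in their allocated arm, using all observed FMA scores at T2, T3 and T4, in a mixed model for repeated measures with arm, visit, arm-by-visit and baseline FMA, without imputation.
- Missing scores are multiply imputed from a model that includes arm and baseline FMA, and the between-arm differences are combined by Rubin's rules within the existing comparison. Rubin's rules need an estimate with a standard error, so this suits the mean difference more directly than the rank test.

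The second option keeps the present comparison; the first changes the analysis model. Either addresses the fault. A delta-adjusted sensitivity analysis would be a useful addition but is optional.

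The cost is wording, a little more analysis work, and confidence intervals that are slightly wider and correct. No patients or visits are added, and MATLAB, already named in {20a}, can fit a mixed model. The Trial status section reports only 2 patients included, so at that stage the change could still be made before outcomes were known.

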### Plans to give access to the full protocol, participant-level data, and statistical code {31c}

Data can be provided to researchers upon request, subject to a review of privacy. Requests for data can be sent to the corresponding author by email. Also all the data will be uploaded in the website of Chinese Clinical Trial Registry.

## Oversight and monitoring

### Composition of the coordinating center and trial steering committee {5d}

The principal investigators (PIs) of this clinical trial are PI # 1, [name], at the Shanghai Seventh People’s Hospital, Shanghai University of Traditional Chinese Medicine, and PI # 2, [name], at the Shanghai Seventh People’s Hospital, Shanghai University of Traditional Chinese Medicine. PI #1 is responsible for designing the research project’s concept, including the stimulation protocol, synaptic-related genes, EEG, and all neurophysiological recording methods. PI #1 will also perform and analyze all neurophysiological recordings for all study participants of the clinical trial along with her research team. PI #2 is responsible for designing radiological and clinical assessments, leading the implementation of visual-auditory stimulation and regular rehabilitation training, as well as conducting clinical assessments for study participants at the hospital. The trial steering committee comprises the PIs and dedicated research staff.

The PIs and dedicated research staff will form the trial steering committee, which is responsible for overseeing and managing the entire project. The study governance for this single-site study is divided into several teams, including the oversight team, recruitment team, intervention deployment and assessment team, neurophysiological recording and neuroimaging team, blood sample team, and data management and analysis team. The oversight team, led by the PIs, has overall responsibility for the conduct and progress of the study. Each team is led by a dedicated research staff or clinician and works closely with the oversight team to establish and monitor standard operating procedures. Each team meets weekly with the PI to discuss decisions and progress within their specific area of responsibility. Full study meetings are held quarterly and as needed to ensure all aspects of the study are coordinated and progressing according to plan.

### Composition of the data monitoring committee, its role and reporting structure {21a}

As visual-auditory stimulation technique is a low-risk intervention which has no substantial safety issues, there will not be a data monitoring committee.

### Adverse event reporting and harms {22}

Due to the low-risk nature of the trial, no adverse event (AE) is anticipated. For very rare cases such as seizure, nausea between study enrollment and hospital discharge will be reported to the Shanghai Seventh People’s Hospital Review Board. The visual-auditory stimulation intervention will be discontinued promptly and professional clinician will provide treatment.

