**Methods:**

This trial is a prospective, randomized controlled, double-blind study. All enrolled patients were randomly assigned to two groups. The experimental group received intervention through 40-Hz visual-auditory stimulation, while the control group underwent intervention with randomly matched visual-auditory stimulation frequencies. The primary efficacy endpoint is the change in motor function. Secondary efficacy endpoints include motor-evoked potentials, cerebral hemodynamic changes, neural network connectivity, and alterations in synaptic-related genes. Safety evaluation included major adverse events, all-cause mortality, and photosensitive epilepsy. Assessments will be conducted at baseline, after a 14-day treatment period, and during subsequent follow-up visits (at 3 and 6 months) post-treatment. The differences between the two groups will be compared.

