### Objectives {7}

This study aims to conduct a prospective clinical trial to validate the safety and effectiveness of the gamma oscillations induced by 40-Hz visual-auditory stimulation in treating patients with post-stroke upper limb dysfunction and explore the relevant mechanisms.

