### Intervention description {11a}

All patients will receive treatment for 25 min per day, 7 days per week for 2 weeks (14 sessions). For all two interventions, the therapists will provide verbal instructions, cues, feedback, and help, when needed.

At a distance of approximately 50 cm from the patient’s eyes, an LED light panel will be positioned. The patient will face to the LED light panel and wear Bluetooth headphones. In this study, an Arduino development board will be employed to control the LED light panel’s signal generator and the playback of specific frequency audio through the headphones. The intervention is demonstrated in Fig. 2

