### Provisions for post-trial care {30}

There is no anticipated harm for visual-auditory stimulation intervention. However, if participants who feel uncomfortable, such as dizziness, nausea, and headache, will be immediately evaluated by the neurologist for further necessary treatment.

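### The only stated adverse event window ends at hospital discharge and covers very rare cases, which does not fit a safety objective with mortality and epilepsy endpoints and visits to 6 months

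*Protocol article*

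**What the plan says.** Three places in the protocol article bear on safety.

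- **Objectives {7}**: the trial is to "validate the safety and effectiveness of the gamma oscillations induced by 40-Hz visual-auditory stimulation", so safety stands beside effectiveness.
- **Abstract, Methods**: "Safety evaluation included major adverse events, all-cause mortality, and photosensitive epilepsy". The same paragraph schedules assessments at baseline, after the 14-day treatment period and "during subsequent follow-up visits (at 3 and 6 months) post-treatment".
- **Adverse event reporting and harms {22}**: "Due to the low-risk nature of the trial, no adverse event (AE) is anticipated". It continues: "For very rare cases such as seizure, nausea between study enrollment and hospital discharge will be reported", to the hospital review board. Stimulation is then to be stopped and treatment given.

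Related text: Intervention description {11a} sets 14 daily sessions over 2 weeks. Provisions for post-trial care {30} anticipates no harm but provides for neurologist evaluation "if participants who feel uncomfortable, such as dizziness, nausea, and headache". The section on non-adherence and missing data {20c} mentions contact with all participants at least weekly. There is no data monitoring committee {21a} and no planned interim analysis {21b}.

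**The concern.** A safety endpoint needs an observation period that is defined in advance and is the same for every patient. All-cause mortality with follow-up to 6 months does not fit a window that closes at discharge. Discharge happens after randomisation and differs between patients, and nothing in the text says that patients stay in hospital for all 14 sessions.

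Restricting the rule to very rare cases, straight after stating that none is expected, adds a second problem. Staff must judge whether an event is rare enough to report, so commoner and milder events may go unrecorded.

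If the section is followed literally, a death or seizure after discharge falls under no stated procedure. A conclusion that the stimulation is safe could then partly reflect what was asked and when. Events not asked about at the time may not be recoverable later.

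**Working it through.** The plan gives no figure for this point, so the check sets the passages side by side.

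1. **Window needed by the endpoints.** The treatment course is 14 days (14 sessions, {11a}). The last visit, T4, is 6 months post-intervention (Table 1 legend; abstract). Taking 6 months as about 182 days, the planned horizon is 14 + 182 = 196 days, nominally the same for each patient.

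2. **Window stated for adverse events.** It runs from enrolment to discharge ({22}). The protocol gives no length of stay, so the stated window has no calendar length, and the share of the 196 days that it covers cannot be derived.

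3. **Does another section fill the gap?**
   - Outcomes {12} and the sections on primary and secondary outcomes list FMA, Brunnstrom, MEP and CMCT, CTP, MRI, EEG and RNA sequencing. The visible text attaches no safety measure to a visit. Table 1 is not shown and may contain one.
   - The abstract places safety evaluation and the visit schedule in consecutive sentences but does not say that safety is assessed at those visits.
   - Weekly contact {20c} is given as a means of knowing participants' condition, under adherence and missing data. It does not mention recording events.
   - The continuous EEG {11a} covers the intervention period only.

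4. **Is the statement that no adverse event is anticipated consistent with the rest?** Section {30} foresees dizziness, nausea and headache. Nausea is also one of the two examples of a very rare case in {22}. The Background describes stroke as having high fatality and recurrence, and patients enter within 1 week of onset. The exclusion for short life expectancy is set at 90 days, whereas follow-up runs to 6 months. Deaths and recurrent strokes are therefore foreseeable in both arms, whatever the device does.

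5. **Effect on the analysis.** Statistical methods {20a} compares categorical variables by chi-squared or Fisher's exact test. For event proportions, that comparison is easy to interpret when every patient is observed over the same period. A window that ends at discharge does not provide this; a fixed one to T4 does, apart from deaths and losses to follow-up.

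**The case against.** The strongest reply is that section {22} is a notification rule. It says what goes to the review board and what happens to the stimulation; it does not say that data collection ends at discharge. The abstract's next sentence schedules assessments at 3 and 6 months, which a reader may fairly take to include safety. Weekly contact would probably bring a death or seizure to light. The abbreviations list defines major adverse events, adverse device effect and a dizziness inventory, which suggests safety content in material not shown. Much of this stands: one cannot say that events after discharge will go unrecorded. What remains is that the only explicit window does not match the stated endpoints, and no visible text says how later events are captured.

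Three stronger readings are tempting and not supported.

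- *That the rule covers only a small, known share of follow-up.* Stays of 14, 21 or 30 days would give 14/196 = 7%, 21/196 = 11% or 30/196 = 15%, but these stays are assumptions. Calendar share is also a poor yardstick for photosensitive epilepsy, because exposure is confined to the sessions.
- *That observation time would differ by arm.* Nothing suggests that length of stay depends on allocation; both arms receive stimulation, and patients and assessors are masked.
- *That the safety conclusion is capped at 9.2%.* Zero events in 31 patients gives a one-sided 95% upper limit of 1 − 0.05^(1/31) = 0.092. That follows from the arm size and an assumed zero count, and would be the same with complete capture to 6 months.

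**Conclusion.** The concern holds as an inconsistency that should be reconciled. The stated adverse event window ends at a patient-dependent discharge and is limited to very rare cases, while safety is a joint objective with mortality, major adverse event and epilepsy endpoints and a last visit 6 months after treatment. The statement that no adverse event is anticipated sits badly with the discomforts that the protocol itself foresees.

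The size of the gap cannot be quantified from the document. The conclusion rests on the visible text only: Table 1 and the full protocol could contain a safety schedule, in which case the remaining task is to bring section {22} into line with it. It would be too strong to infer that a finding of safety would be produced by the window alone.

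**What to change.** Amend Adverse event reporting and harms {22} so that:

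- all adverse events, seizures and deaths are recorded and reported from enrolment to T4, in every patient and both arms. The start should remain enrolment, since starting at the first session would lose events that the present rule covers;
- events are asked about in the same way at the existing sessions, weekly contacts and T2, T3 and T4 visits;
- events are compared by arm over that common window, with confidence intervals from the events actually observed and no limit fixed in advance;
- the statement that no adverse event is anticipated, and the restriction to very rare cases, are removed.

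The abstract, {12} and {20c} should then point to this one window. The change concerns recording and reporting only and leaves clinical management as it is. It costs a short set of questions at contacts that already take place, and one amendment. With 2 patients included at the time of the Trial status statement, making it early would keep most of the sample under a single rule.
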